The immune response to conjugated vaccines with or without CpG ODN has been tested in studies on mice. Chu et al. used conjugated pneumococcal antigen from the Prevenar vaccine and found a 23-fold increase in total antibody response when a CpG ODN was administered with the vaccine compared to the conjugated vaccine alone{{142 Chu,R.S. 2000; }}. Studying the adjuvant effect of CpG ODN with conjugated Haemophilus influenzae type b (Hib) vaccine (using the same carrier as in Prevenar(CRM)) von Hunolstein et al. found a superior immune response when a CpG was added to the vaccine{{148 von Hunolstein,C. 2001; }}. In a study of CpG and pneumococcal vaccine Kovarik et al. found no additive effect of CpG to plain polysaccharide antigen (as used in the Pneumo Novum vaccine){{147 Kovarik,J. 2001; }}. They found an age and serotype-dependent effect of adding CpG to conjugate pneumococcal antigens (using a tetanus toxoid as carrier). The increase in serotype-specific antibodies was only observed in adult mice and was largely dependent on CD4+ cells. Similar results were observed in another study where adding CpG to a conjugated pneumococcal vaccine restored aged mice’s immune response levels to that of young adult mice{{143 Sen,G. 2006; }}. This finding was also linked to CpG ODNs ability to augment CD4+ T-cell help. As depletion of CD4+ T-cells is a key component in the progression of HIV, we hypothesize that the addition of a CpG ODN to a pneumococcal vaccine would be particularly useful in HIV-infected patients.

The optimal time in the course of the disease for immunization of HIV infected individuals is debated. The general opinion is that the sooner - the better, although it’s recognized that patients with low CD4 count (i.e. less than 200) benefit little from vaccination. In this study we have decided to include HAART naïve (individuals who not yet begun antiretroviral treatment) as well as HAART experienced individuals to study and compare vaccination effects in both groups. In relation to CPG 7909 this raises a possible safety issue.

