TLR9 activation with bacterial DNA can induce the HIV transcriptional regulatory elements in long terminal repeats (LTRs){{152 Equils,O. 2003; }}, increasing viral replication. HIV-infected humans treated systemically with a B-class ODN that contained a CpG motif showed dose-dependent increases in plasma HIV branched DNA levels, which represent the level of virus in the blood{{153 Agrawal,S. 2003; }}. However, 6 days after the last CpG-infusion plasma HIV had returned to placebo-treated individual’s levels and the magnitude of viremia was dose dependent (no effect on viral replication was observed for low doses CpG). It is important to note that in this study, the CpG ODN was administered in high doses (the lowest dose was 3.2 mg/kg/day, and the highest dose was 4.4 mg/kg/day by continuous intravenous infusion for 8 days, whereas when used as a vaccine adjuvant it is administered IM at a dose of approximately 0.01 mg/kg Furthermore, despite their capacity to induce HIV transcription, CpG ODN can also show anti-HIV activity: the high level of IFN-α-production induced by A-class ODN suppresses HIV replication in human foetal thymus cells{{154 Gurney,K.B. 2004; }}, and B-class ODN can also suppress HIV replication in cultured human cells, albeit in a sequence-independent fashion{{155 Schlaepfer,E. 2004; }}.

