Transient increases in HIV viral load have been observed in relation to a variety of immune stimulating events such as flu-vaccination{{160 O'Brien,W.A. 1995; }}, tetanus-vaccination{{163 Stanley,S.K. 1996; }}, oral-cholera-vaccination{{161 Ortigao-de-Sampaio,M.B. 1998; }} and during acute infectious illnesses{{162 Sulkowski,M.S. 1998; }}. IL-2 treatment in humans induces transient increases in HIV DNA but does not promote virological failure or emergence of resistance{{156 Delaugerre,C. 2003; }}. Several recent reviews have concluded that viral load blips (small transient increases in viral load) are not typically associated with the development of resistance mutations and more importantly are not associated with virological or clinical failure of previously adequate HAART{{158 Lee,P.K. 2006;157 Di Mascio,M. 2003; 159 Nettles,R.E. 2005; }}. Furthermore acute infectious illnesses and vaccination has been shown not to induce virological failure or emergence of resistance{{157 Di Mascio,M. 2003;159 Nettles,R.E. 2005; }}. In the Engerix B (+ CPG 7909) trial with 38 HIV infected individuals, no changes in HIV RNA were observed in the CPG 7909 group versus the control group{{41 Cooper,C.L. 2005; }}.Thus, we consider it unlikely that a small intramuscular dose of CPG 7909 should induce virological failure, emergence of resistance or persistent viremia.

CPG 7909 is currently being evaluated as adjuvant to a novel malaria vaccine candidate and is also being tested in a number of cancer treatment trials{{96 US NIH 2007; }}. Searching the US National Institutes of Health (NHI) website of registered clinical trials (www.clinicaltrials.gov) revealed a total of 31 human clinical trials using CPG 7909 and CPG 10101. Ten of the studies were ongoing trials and the rest completed or no longer recruiting patients. More than 2000 subjects were included in the trials receiving one or multiple doses CpG, and subcutaneous injections of up 40 mg CPG 7909 were administered.

A different CpG ODN manufactured by Dynavax was registered in another 5 trials of which the largest – a phase III trial of a novel CpG adjuvanted hepatitis B vaccine (HEPLISAV™) – had an expected total enrolment of 1740 individuals. In all the studies of TLR9-agonists the maximal tolerated dose in humans has never been reached {{40 Krieg,A.M. 2006; }}. Therefore a dosing of 1 mg CPG 7909 with each pneumococcal vaccination appears safe and well below the upper limit used in other TLR9-agonist trials.

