**TEST DRUG AND PLACEBO PREPARATION**

Vial fills of 1.0ml (10mg/ml) CPG 7909 will be shipped from Coley Pharmaceutical Group. The Hospital Pharmacy at Århus University Hospital will import, prepare and label CPG 7909 and placebo as described below. The primary investigator will advise the Hospital Pharmacy of the required amount of doses needed by faxing a complete list of study participants (by study IDs) one day before the participants are scheduled to come. The Hospital Pharmacy is responsible for the safe and appropriate storage of CPG 7909 and placebo until the doses are dispatched to the sponsor/investigator. Upon receipt of the syringes at The Department of Infectious Diseases the sponsor/investigator takes full responsibility for the safe and appropriate storage of the preparations. The Hospital Pharmacy guarantees drug sterility for 24 hours after dispatch.

TREATMENT AND STORAGE OF VACCINES, TEST DRUG AND PLACEBO

Vaccines will be kept in a refrigerator at 5° Celsius in a clearly marked rack at the Department of Infectious Diseases. Test drugs and placebo will be kept on a separate rack in the same refrigerator in identical 1 ml syringes.

**OTHER TREATMENT:** No additional medication or treatment is planned and no changes in regular medication will be made due to the participant’s inclusion in this study. Any changes in medication during the time of the study will not disqualify the individual for further participation in the study and study participation will not interfere with the HIV physician’s decision regarding HAART and other medical treatment received or initiated during the time of the study.

**ROUTE OF ADMINISTRATION:** Intramuscular injection

**BLINDING:** Double-blinded study.

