**SECONDARY ENDPOINTS:**

**REACTOGENICITY AND SAFETY IN ALL SUBJECTS**

**ANALYSIS POPULATIONS:**

**Safety population:** all patients who received at least one vaccination.

- Occurrence of solicited and general symptoms during the 4-day (day 0 to Day 3) period after each vaccination dose
- Occurrence of unsolicited symptoms up to 1 month after each vaccination
- Changes in CD4-count and viral load during the study

Safety will be assessed by physical examination, adverse events (according to common toxicity criteria version 2.0), laboratory tests, and HIV control parameters (HIV RNA and CD4-count).

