# SCHEDULE OF ASSESSMENTS/PROCEDURES

| **Assessments/ Procedures** | **Baseline** | **Vaccination** | | | **Follow-up** | | | |
| --- | --- | --- | --- | --- | --- | --- | --- | --- |
| **Study Day** | **Predose** | **Day 0 (1)** | **Day 90 ± 14 (2)** | **Day 270 ± 30 (2)** | **Day 90 ± 14 (3)** | **Day 270 ± 30 (4)** | **Day 300 ± 30 (4)** | |
| Written Informed Consent | X |  |  |  |  |  |  | |
| Inclusion/Exclusion Criteria | **X** |  |  |  |  |  |  | |
| Medical History and Demographics | **X** |  |  |  |  |  |  | |
| Pregnancy Test**(5)** | **X** |  | **X** | **X** |  |  |  | |
| Randomization | **X** |  |  |  |  |  |  | |
| Conjugate pneumococcal vaccine ± CPG 7909 **(6)** |  | **X** | **X** |  |  |  |  | |
| Polysaccharide pneumococcal vaccine ± CPG 7909 **(6)** |  |  |  | **X** |  |  |  |  |
| **Safety** |  |  |  |  |  |  |  | |
| Physical Examination |  | **X(7)** | **X(7)** | **X(7)** | **X(8)** | **X(8)** | **X(8)** | |
| Bloodpressure and Heartrate |  | **X(7)** | **X(7)** | **X(7)** | **X** | **X** | **X** | |
| Lab Safety Tests**(9, 10)** | **X** |  |  |  | **X** | **X** | **X** | |
| HIV Control Parameters**(11)** | **X** |  |  |  | **X** | **X** | **X** | |
| Adverse Events**(12)** |  | **X** | **X** | **X** | **X** | **X** | **X** | |
| **Efficacy** |  |  |  |  |  |  |  | |
| Functional antibody response | **X** |  |  |  | **X** | X | X | |
| Quantitative antibody response | **X** |  |  |  | **X** | **X** | **X** | |
| Oropharyngeal swap | **X** |  |  |  |  | **X** | **X** | |
| Immunologic markers **(13)** | **X** |  |  |  | **X** | **X** | **X** | |

1. Day 0 vaccination is conducted after all baseline assessments/procedures are made.
2. Day 90 follow-up and vaccination can vary by 14 days
3. Follow-up is done before proceeding to 2nd vaccination
4. Follow-up day 270 and day 300 is allowed to vary by 30 days.
5. Women of childbearing potential only.
6. According to randomization.
7. Participants asked to stay in for at least ½ hour post-vaccination. A physical examination incl. BP and HR will be made before discharge.
8. Physical examination will be made on participants request or if the investigator finds it relevant.
9. Complete bloodcount, serum chemistry and liver parameters
10. If a participant withdraws prematurely, lab safety tests must be done within approximately one week of participant withdrawal
11. Viral load (HIV RNA) and CD4-count

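### Viral-load and CD4 changes are compared between arms in all vaccinated subjects, diluting an effect confined to untreated patients; the sampling days support conclusions on persistent change only

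*Protocol*

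**What the plan says.** The Background explains that HAART-naive and HAART-treated patients are both enrolled and adds: "In relation to CPG 7909 this raises a possible safety issue". The mechanism follows: "TLR9 activation with bacterial DNA can induce the HIV transcriptional regulatory elements", with more viral replication as the result. The human evidence cited is a high-dose intravenous infusion study, in which "6 days after the last CpG-infusion plasma HIV had returned" to the level seen under placebo. The section closes by judging it unlikely that a small intramuscular dose "should induce virological failure, emergence of resistance or persistent viremia".

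Under Analysis Populations, the safety endpoint is "Changes in CD4-count and viral load during the study", in a section covering all subjects and a safety population of everyone given at least one vaccination. The data-evaluation section compares all endpoints between the two vaccine arms and adds a substudy of on-HAART against no-HAART patients, which it calls non-randomised.

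Exclusion criterion 5 removes on-HAART patients above 50 copies/mL; untreated patients have no viral-load limit. Under Other Treatment, "Any changes in medication during the time of the study will not disqualify the individual for further participation in the study", and the treating physician remains free to start HAART. The case report form records medication changes.

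The Schedule of Assessments places the HIV control parameters (footnote 11: "Viral load (HIV RNA) and CD4-count") at baseline and at the day 90, 270 and 300 follow-ups. The day 90 follow-up precedes the second vaccination. Doses are given on days 0, 90 and 270.

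**The concern.** The safety question is sharpest in untreated patients, whose viral load is free to rise. The one between-arm comparison that the protocol states averages them with patients who start at or below 50 copies/mL. The HAART substudy does not repair this: it contrasts treated with untreated patients, not CPG 7909 with placebo within either group. Adjusting for baseline HAART status does not repair it either. Without an interaction term, and with 1:1 allocation within strata, the adjusted estimate is still an average of the two stratum effects weighted by their size.

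HAART started on study lowers viral load and raises CD4, and no rule for it appears. Separately, the sampling days determine which kind of rise the trial can see. An overall result near zero could be taken as evidence against both a transient rise and an effect in untreated patients, although the comparison is weak on the second and has no designed view of the first.

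**Working it through.** **Sample size.** The protocol gives no power figure for viral load. Its primary-endpoint figure reproduces: for 30% against 60%, two-sided alpha 0.05 and 80% power, n = [1.960 x sqrt(2 x 0.45 x 0.55) + 0.842 x sqrt(0.21 + 0.24)]^2 / 0.30^2 = 42 per group. Then 42/0.90 rounds up to 47 per arm, or 94 in total.

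**Dose-to-sample gaps** (dosing days and Schedule of Assessments):
- Dose 1 (day 0) to day 90: 90 days; window 76 to 104.
- Dose 2 (day 90) to day 270: 180 days; window 136 to 224.
- Dose 3 (day 270) to day 300: 30 days nominally, and up to 90 if the two 30-day windows are read independently. Those windows overlap, so an individual gap could also be shorter than 30 days, but not by design.

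Against the cited 6 days, the nominal gaps are 15, 30 and 5 times as long.

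**Dilution.** The randomisation section starts untreated patients at ID 1 and on-HAART patients at ID 43. With 94 enrolled and all IDs filled, that is 42 untreated (21 per arm) and 94 - 42 = 52 on HAART (26 per arm). If the effect is d in untreated patients and zero on HAART, the overall difference is (42/94) x d = 0.45d. If only half the untreated IDs were filled and 94 were still enrolled, it would be (21/94) x d = 0.22d.

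**Precision in untreated patients** (illustrative). Assumptions not in the protocol: SD of log10 change 0.3 to 0.5 in untreated patients and 0.1 on HAART; a fall of 2.5 log10 after starting HAART; a share f of untreated patients starting, equal in both arms; no drop-out.

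Untreated stratum alone: s = sqrt(SD^2 + f(1-f) x 2.5^2), and detectable difference = 2.802 x s x sqrt(2/21). Overall, unadjusted comparison: with w = 42/94 and m = -2.5f, variance = w(s^2 + m^2) + (1-w) x 0.1^2 - (wm)^2, and the effect needed in untreated patients = 2.802 x sqrt(variance) x sqrt(2/47) / w.

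| Share starting HAART | Stratum alone (log10) | Needed in untreated patients if pooled (log10) |
|---|---|---|
| 0% | 0.26-0.43 | 0.28-0.44 |
| 10% | 0.70-0.78 | 0.72-0.80 |
| 20% | 0.90-0.97 | 0.96-1.02 |
| 30% | 1.02-1.08 | 1.14-1.19 |

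Varying the assumed fall at 20% starting, stratum alone: for 2 log10, s = sqrt(0.09 + 0.64) to sqrt(0.25 + 0.64), giving 0.74 to 0.82; for 3 log10, s = sqrt(0.09 + 1.44) to sqrt(0.25 + 1.44), giving 1.07 to 1.12.

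Pooling itself costs little power. It shrinks the reported difference and obscures whom it describes. HAART starts cause most of the loss of precision.

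**What the schedule can show.** If none of 26 suppressed patients in an arm rose above 50 copies/mL, the one-sided 95% upper bound would be 1 - 0.05^(1/26) = 10.9%. Persistent loss of suppression is observable, with limited precision.

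**The case against.** A reader might infer that the endpoint cannot answer the protocol's safety question at all. The documents do not support that. The Background ends on virological failure, resistance and persistent viraemia, and HIV RNA on days 90, 270 and 300 can show failure and persistent viraemia, most clearly in patients suppressed at entry. The 6-day figure comes from continuous infusion at 3.2 to 4.4 mg/kg/day, against about 0.01 mg/kg intramuscularly for a vaccine adjuvant, and the Background reports no effect on replication at low doses. It also cites a hepatitis B vaccine trial of CPG 7909 in 38 HIV-infected individuals with no HIV RNA change, although the reference list titles that trial as one in antiretroviral-treated adults, so it does not speak for the untreated stratum.

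A reader might also infer that HAART starts would create a false treatment difference. Allocation is randomised, blinded and balanced on HAART status, so starts are mainly noise. They bias the contrast only if starting depends on arm, for example if a rise in viral load prompts treatment, in which case the later fall would hide the harm.

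Finally, covering all subjects is a population definition, not an explicit instruction to average the strata; safety data are to be listed and summarised, and stratum tables may sit in an analysis plan not shown. That stands as far as it goes. But the between-arm comparison is the only one the protocol states for CPG 7909, and the sampling days are protocol content.

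**Conclusion.** The point holds in a limited form. The stated comparison mixes two groups with different entry viral loads and different scope for change, and would show about 45% of an effect confined to untreated patients. That figure assumes the ID numbering reflects actual enrolment, which the protocol does not set as a target. By design, the schedule would miss a rise lasting days. It can show persistent viraemia and virological failure.

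The log10 figures rest on assumed SDs, an assumed fall and assumed shares starting HAART; they indicate direction and rough size only. Nothing here shows that CPG 7909 raises viral load at the adjuvant dose, or that the trial's virological safety data are without value.

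**What to change.** 1. Compare CPG 7909 with placebo within each HAART randomisation stratum: log10 HIV RNA and CD4 change in the no-HAART stratum, and the proportion above 50 copies/mL in the on-HAART stratum.
2. Report the number and timing of HAART starts by arm as a safety outcome. Show no-HAART results with all values and, as a sensitivity analysis only, with values up to HAART start. Truncation must not be the main analysis, because it would discard later values if a rise in viral load led to treatment.
3. State that the viral-load safety conclusion concerns persistent change, not transient viraemia.

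No additional sampling is needed for these changes. The cost is wording and tabulation, since randomisation already separates the strata and the case report form records medication changes. The downside is smaller numbers per stratum (about 21 and 26 per arm if the ID list is filled), a main no-HAART analysis that stays imprecise if many start HAART, and a narrower safety claim.

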**STATISTICAL ANALYSES**

**Baseline characteristics**

Differences between study groups at day 0 will be assessed by Mann-Whitney rank sum test (continuous variables) and Chi-square test (dichotomous and categorical variables).

**Primary endpoint**

Prevalence ratios of high responders at six months after 2nd vaccination with Prevenar, comparing the two vaccination scheme groups (with/without CPG 7909), will be estimated by Poisson regression adjusted by age, CD4 cell count at baseline and HAART (on HAART vs. no HAART) at baseline.

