##### ENROLMENT: Randomization;

Eligible patients will be randomized in a ratio of 1:1 to receive **pneumococcal vaccination with or without CPG 7909**. Random allocation lists will be generated by computer by the hospital pharmacy. A complete randomization list will be stored at the hospital pharmacy. Cluster randomization will be used to obtain similar distributions of on-HAART and HAART-naïve subjects in the two treatment arms. Subjects will be randomized in blocks of 6. Sealed envelopes revealing the subjects’ treatment allocation will be made by the Hospital Pharmacy and transferred to a safe at the Department of Infectious Diseases before initiating the study. If indicated (i.e. in the case of a SUSAR (see below)) a subject’s group allocation can be revealed without unmasking the entire study.

Participants will receive their study ID after passing inclusion/exclusion criteria (according to treatment; +HAART/-HAART). Participants will be entered into the study and given study ID according to the chronological order in which they are included (i.e. the first subject in the study will be assigned study ID #1 if HAART naïve, or study ID #43 if on HAART, the 2nd subject will receive the next available study ID according to HAART status and so fort). Registration is done by the investigator by highlighting the next available number on the entry list and by adding randomization labels to the front of the subjects CRF. Participants will be blinded to their assigned vaccine adjuvant (placebo or CPG 7909). Investigators conducting the immunization will also be blinded to the subject’s treatment allocation and to the contents of the test drug/placebo preparation.

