**Secondary endpoints**

Comparison of endpoints between the study groups will be done by Poisson regression (dichotomous endpoints) or linear regression (continuous endpoints), adjusted for appropriate potential confounders.

Predictors for achieving a high vaccination response (classified as a high responder) at six months after 2nd vaccination with Prevenar will be estimated by multivariate Poisson regression.

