##### ESTIMATED SAMPLE SIZE

**Intention-to-treat (ITT) population:** all randomized participants

Sample size is calculated for the primary endpoint (prevalence ratios of **high responders at six months after 2nd vaccination with Prevenar**, comparing the two vaccination scheme groups). Setting the probabilities of Type I and Type II error to:

- Type I error probability (a) = 0.05 (two-sided).
- Type II error probability (ß) = 0.20 (power = 1 - ß = 0.80).
- Primary endpoint: proportion of vaccine highresponders (defined as2-fold increase and IgG levels ≥1 µg/mL to at least 5 of 7 pneumococcal serotypes).
- N is the number of participants needed in each group.

| Control\CpG | 0.50 | 0.55 | 0.60 | 0.65 | 0.70 |
| --- | --- | --- | --- | --- | --- |
| 0.20 | 39 | 29 | 23 | 18 | 15 |
| 0.25 | 58 | 41 | 31 | 24 | 19 |
| 0.30 | 93 | 61 | **42** | 31 | 24 |
| 0.35 | 170 | 96 | 62 | 43 | 31 |
| 0.40 | 388 | 173 | 97 | 62 | 42 |

Assuming a prevalence of 30% in control vaccine the group and a prevalence of 60% in the experimental vaccine group a sample size of 42 patients per group is required to detect a difference in prevalence estimated by Poisson regression. The expected drop-out percentage is set to 10%. Thus, a total of 94 subjects are needed in the study.

In accordance with the approach recommended by regulatory authorities, the two-sided 95% confidence interval (CI) of the immune response difference will be calculated.

Should the targeted number of participants not be reached within 12 months from study initiation the primary investigator can decide to stop the study if he considers reaching the expected 94 patients unlikely under the given circumstances. In that case all statistical analysis will then be based on the number of patients included at the time of study termination.

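### Poisson regression is named for a yes/no primary endpoint with no robust variance, while the 42 per group credited to it comes from a binomial two-proportion formula; with default standard errors power would be about 54%, not 80%

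*Protocol*

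**What the plan says.** The primary endpoint is binary: each participant either is or is not a high responder six months after the second conjugate vaccine dose.

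- **Statistical Analyses, Primary endpoint.** The effect measure is the prevalence ratio between the two arms, which "will be estimated by Poisson regression adjusted by age, CD4 cell count at baseline" and baseline HAART status. No variance estimator is named.
- **Statistical Analyses, Secondary endpoints.** Poisson regression is also assigned to the dichotomous secondary endpoints. Predictors of high response "will be estimated by multivariate Poisson regression". Again no variance estimator is named.
- **Estimated Sample Size.** Two-sided alpha is 0.05 and power 0.80. "Assuming a prevalence of 30% in control vaccine the group and a prevalence of 60% in the experimental vaccine group", the protocol concludes that "a sample size of 42 patients per group is required to detect a difference in prevalence estimated by Poisson regression". A 10% drop-out allowance brings the total to 94. The same section adds that "the two-sided 95% confidence interval (CI) of the immune response difference will be calculated".

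**The concern.** A Poisson model takes the variance of each observation to be its mean, p. A yes/no outcome has variance p(1 − p). At low prevalence the two nearly agree, but at 30% to 60% they do not, and the default standard errors are clearly too large. The point estimate of the prevalence ratio is unaffected; the confidence interval and the p-value are affected.

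The Estimated Sample Size section makes a checkable statement, that 42 per group gives 80% power for Poisson regression. If the number rests on one variance and the default form of the named method uses another, the stated power does not belong to the analysis as named. Enrolment stops at 94 and withdrawals are not replaced, so the sample size leaves no room to absorb a large loss of power. The dichotomous secondary endpoints and the predictor analysis carry the same wording.

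**Working it through.** **Inputs (Estimated Sample Size; 1:1 allocation from the Randomization section).** Control 0.30, CPG 7909 0.60, ratio 2.0, two-sided alpha 0.05, power 0.80, drop-out 10%.

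**1. Reproduce the 42.** Pooled two-proportion formula without continuity correction, with mean proportion 0.45:

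n = [1.96·√(2·0.45·0.55) + 0.8416·√(0.30·0.70 + 0.60·0.40)]² / 0.30²
= [1.96·0.7036 + 0.8416·0.6708]² / 0.09 = 1.9435² / 0.09 = 41.97, so **42**.

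The same formula reproduces all 25 cells of the table. With continuity correction this cell would be 49, which does not match. Drop-out: 42 / 0.9 = 46.7, so 47 per group and 94 in total. The protocol's figures are therefore right for a two-proportion test. No Poisson variance enters them.

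**2. Standard error of the log prevalence ratio at 42 per group.** Expected responders are 12.6 and 25.2.

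- Poisson, model-based: √(1/12.6 + 1/25.2) = 0.345
- Binomial, which the robust variance estimates: √(0.7/12.6 + 0.4/25.2) = 0.267
- Ratio: 0.345 / 0.267 = 1.29, about 29% too large

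**3. Power by normal approximation.** With model-based errors the test rejects when the log ratio exceeds 1.96·0.345 = 0.676. The true log ratio is ln 2 = 0.693 with true standard deviation 0.267. Power = Φ[(0.693 − 0.676)/0.267] = Φ(0.06), about 52.5%. With robust errors: Φ(0.693/0.267 − 1.96), about 74%.

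**4. Exact binomial enumeration, 30% versus 60%, unadjusted tests.**

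| Per group | Poisson, model-based Wald | Poisson, robust Wald | Chi-square |
| --- | --- | --- | --- |
| 42 | 54.1% | 76.7% | 82.8% |
| 47 | 60.1% | 84.2% | 84.2% |

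A likelihood-ratio test from the Poisson model gives 57.1% at 42. With model-based errors, 67 per group would be needed to reach 80%.

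**5. Type I error at 42 per group, both arms at the same prevalence.** Model-based Wald: 1.7% at 0.30, 0.8% at 0.45, 0.2% at 0.60. Robust Wald: 4.1%, 3.7%, 4.2%.

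**6. Covariate adjustment.** Simulation of the adjusted model used 3,000 runs per setting, with age and CD4 as standardised normal variables and HAART at 50%. The covariates had either no effect or modest assumed effects, since the protocol gives no values. Power at 42 per group was 52% to 54% with model-based errors and 78% to 83% with robust errors. Adjustment does not remove the problem.

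**7. One data set near expectation.** With 13/42 versus 25/42 the ratio is 1.92. The model-based 95% interval is 0.98 to 3.76 and the robust interval 1.15 to 3.22.

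**The case against.** The strongest reply is that the protocol names a model and an effect measure but no standard error. Poisson regression gives a valid prevalence ratio for binary data, and the trouble arises only with default errors. The choice of variance estimator is commonly left to a statistical analysis plan, and none is at hand here. The table's binomial variance can even be read as planning for an analysis that respects it, as robust Poisson regression does. On that reading 42 per group is about right. Sizing a regression analysis by a two-proportion formula is also a common approximation.

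Much of this stands. A reader might infer that the trial's real power is 54%. The text does not support that without the condition of default standard errors. What remains is that the sample size section ties its 42 and its 80% to Poisson regression, while the arithmetic behind them is a different method, and that nothing in the protocol steers the analyst away from the default.

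A reader might also infer that promising an interval for the difference alongside a prevalence ratio is a second error, because the two could disagree. At the design assumption and 42 per group, the difference interval excludes 0 while the model-based ratio interval includes 1 in about 29% of trials. With robust errors this falls to about 6%, and to 0.2% at 47 per group. The disagreement is thus mostly a consequence of the variance problem. Both the primary analysis and the sample size section already name the ratio for the primary endpoint, and reporting an absolute measure beside it is not a contradiction.

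Finally, the error cannot produce a false claim of benefit. That limits its seriousness but does not remove the loss of power.

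**Conclusion.** The concern holds in conditional form. The 42 per group is a two-proportion sample size that the protocol attributes to Poisson regression. If the model is run as named with default standard errors, power for 30% versus 60% is about 54% at 42 per group and 60% at 47, against the stated 80%. True type I error is then about 0.2% to 1.7% for common prevalences of 0.60 down to 0.30. A true doubling of the response rate would be missed in nearly half of such trials.

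With robust errors most of the loss disappears, although unadjusted power at 42 is nearer 77% than 80%.

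These figures rest on the protocol's own response rates and on Wald tests; the adjusted figures also rest on assumed covariate effects. The error costs power and precision only. It gives no reason to change the sample size.

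**What to change.** - **Primary endpoint and Secondary endpoints:** specify Poisson regression with robust (sandwich) standard errors for every yes/no endpoint, including the predictor analysis. Keep the primary model's covariates as they are.
- **Estimated Sample Size:** state that 42 per group comes from the two-proportion formula without continuity correction. Restate power for the robust analysis at 30% versus 60%: about 77% unadjusted at 42 evaluable per group, roughly 78% to 83% in adjusted simulations, and 84% unadjusted at 47. Leave the total at 94.
- **Minor clarification:** say that the prevalence ratio is the primary measure and the interval for the difference is supportive.

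The cost is wording and one option in the model call. No participants, visits or data are added. The stated power at 42 evaluable per group becomes slightly less favourable on the unadjusted figure.
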